## Abstract

**Introduction:**

Older stroke survivors usually experience various psychology disorders, such as post-stroke depression (PSD), which may be associated with high experiential avoidance (EA) and can seriously affect their quality of life. To date, the efficacy of group-based acceptance and commitment therapy (ACT) for older stroke survivors has not been established. The aim of this study is to investigate the effectiveness of group-based ACT on EA, PSD, psychological distress, and quality of life in older stroke survivors after group-based ACT.

**Methods and analysis:**

This study is a randomized, single-blind, wait-list controlled, parallel-arm trial. A total of 66 stroke survivors will be randomly assigned to wait-list control group or intervention group. Participants in wait-list control group will receive treatment as usual (TAU), while the intervention group will receive group-based ACT once a week for eight weeks. The primary outcome measure being EA, and the secondary outcome measures being PSD, psychological distress, and quality of life. Results of the two groups will be blindly assessed by professional evaluators at baseline (T0), post-treatment (T1), and one-month follow up (T2).

**Discussion:**

The results of this study will provide the first evidence for the effectiveness of a group-based ACT intervention in reducing EA, PSD, psychological stress, and improving quality of life for post-stroke survivors.

**Trial Registration:**

ChiCTR2200066361.

**Supplementary Information:**

The online version contains supplementary material available at 10.1186/s12906-023-04160-z.

## Introduction

The global prevalence and incidence of stroke have increased significantly [1]. The prevalence of stroke increases with age, especially among the older patients [2]. According to the data obtained from 1,672 Chinese tertiary public hospitals, the average age of the 3,411,168 stroke cases during 2019 was 66 years old [3]. As treatment techniques continue to advance, more and more older stroke patients are expected to survive through active treatment. There are about 2.4 million new stroke patients and about 11 million stroke survivors in China every year [2, 3].

After surviving through the acute treatment, many older stroke survivors would be left with obvious complications such as cognitive, motor and sensory dysfunctions. They are often subject to partial or total loss of self-care ability, and are unable to play family and social roles, resulting in series of negative emotions [4–6]. Compared with stroke survivors in other age groups, older patients have poorer mobility, significantly reduced cognitive function and difficulty in regulating psychological distress. Therefore, subjectively, they may attempt to get rid of, avoid and escape from the previous painful experience of illness, and are unable to actively participate in social functional activities in accordance with their personal value goals, in a bid to restore their physical functions and return to normal life, which can be defined as experiential avoidance (EA) [7].

EA is essentially an avoidant coping process in which individuals associate certain cognitive and environmental cues with physiological and psychological discomfort and subsequently attempt to distance themselves behaviorally or psychologically from the discomfort [7]. Although it provides relief in the short term, it can sustain and often exacerbate psychological problems in the long term [8]. Studies have shown that the older persons are less likely to seek advice or to use strategies such as information seeking and emotional expression in the face of chronic illness, and tend to opt for fact-avoidance and behaviors that may stem from avoidance processes [9]. It is easy to imagine that within this context, painful emotional experiences would be suppressed or avoided altogether, and avoidance-based coping strategies in particular could become more prominent among older stroke survivors, which may lead to long-term mental health problems [10]. Therefore, EA may be an important predictor of mental health problems among the older stroke survivors, and may function as both an etiological and maintaining factor of post-stroke depression [10].

The most common neuropsychiatric outcome in stroke survivors is post-stroke depression (PSD) [11]. A meta-analysis of stroke survivors showed that PSD was the most common predictor of quality of life in stroke survivors [12]. Some studies suggest that PSD is longer, more severe and more difficult to treat [13], which may be related to the psychological rigidity and inflexibility of stroke survivors. Both the changes brought about by the disease and the psychological distress can significantly reduce the quality of life [5, 6, 14], thus increasing the risk of stroke recurrence and even death [15, 16]. With the transformation of the bio-psycho-social medical model, the rehabilitation of older stroke survivors has mainly focused on reducing the level of PSD and psychological distress, improving psychological resilience, and improving the quality of life. How to improve the physical and mental status of older stroke survivors, alleviate negative emotions, and improve their quality of life, has become an imperative problem to be solved by more and more scholars [17–19].

The Canadian Stroke Best Practice Recommendations, CSBPR) state that psychotherapy, including cognitive behavioral therapy, is one of the most commonly used strategies for post-stroke depression [16]. Acceptance and commitment therapy (ACT), referred to as the third wave of CBT, is a kind of behavioral therapy based on functional contextualism and relational framing theory [20]. The core component and the ultimate goal of ACT theory is to improve the individual’s psychological flexibility [21], that is, to fully feel, perceive and accept the things and emotions you experience at the moment, rather than focusing on avoiding painful memories or negative emotions in reality, and to make behavioral changes according to the direction of their own values, so as to change the relationship between cognition and emotion. ACT has been increasingly used in the psychological aspect of stroke survivors [5, 22, 23]. It can effectively relieve the psychological distress of stroke survivors and improve their quality of life, which may be related to ACT’s ability to reduce patients’ EA and improve their psychological flexibility.

In groups, people can socialize with peers with similar symptoms, have the opportunity to improve one’s altruism and empathy, and feel useful by helping others. In addition, group therapy results in a more cost-effective professional/client ratio [24]. In particular, group therapy provides an opportunity for depressed older adults, who often live in isolation and have lost significant relationships, capacities, or occupations, to once again feel connected with and useful to the society, as well as to (re)discover their meaning in life. Therefore, group-based ACT may have more unique therapeutic benefits, such as reducing feelings of isolation, providing opportunities to learn from the experience of other attendees, and developing new coping strategies and behavioral patterns based on such shared learning for older stroke survivors in China.

A study by Niu et al. [23] showed that group-based ACT could effectively relieve depressive symptoms and improve neurological function in PSD, thereby improving the quality of life of patients. One research supported the applicability of the ACT core processes in a variety of clinical populations, including older people [25]. Although relevant psychological studies have been carried out in the older population, and there are studies of group-based ACT for post-stroke depression, the application effect of group-based ACT in Chinese older stroke survivors needs to be further explored. Whether group-based ACT can be used as a supplementary study of TAU to enhance the psychological health of older stroke survivors has not been confirmed. This study aims to investigate the effectiveness and applicability of the group-based ACT intervention for older stroke survivors based on previous studies.

Therefore, we propose the following hypotheses: (1) ACT is an effective cognitive and behavioral intervention to improve EA, PSD, psychological distress, and quality of life of older stroke patients; and (2) compared with TAU alone, the group-based ACT may have better results on the psychological status of the older stroke survivors.

## Methods and analysis

### Patient and public involvement

No patient involved.

### Study design

This study is a randomized, single-blind, wait-list controlled, parallel-arm trial. Older stroke survivors will be selected from a tertiary hospital in China using convenience sampling between December 2022 to March 2023. Older stroke survivors who meet the inclusion criteria will be informed of the purpose and methods of the study and sign the informed consent forms through face-to-face communication. Then, they will be randomly assigned to either a wait-list control group (TAU group) or an intervention group (group-based ACT group). EA, PSD, psychological distress and quality of life of patients will be blindly evaluated at baseline (T0), post-treatment (T1), one-month follow up (T2) for both groups (see Fig. 1).

**Fig. 1 Fig1:**
[figure not shown]
Flow diagram of the study

Through literature review, qualitative interviews and group discussions, this study established an initial intervention program of group-based ACT for older stroke survivors. Two rounds of Delphi expert consultations were conducted on the group-based ACT program via email for initial intervention program. The recovery rates of expert questionnaires in the two rounds were 70% and 100%, respectively, with Ca standing at 0.95, Cs at 0.87 and Cr at 0.91, indicating that the authority of experts was high and the reliability of consultation results was effectively guaranteed. The Kendall’s W coefficients of the two rounds were 0.130 and 0.126 respectively (P < 0.05), and the experts’ opinions tended to be consistent.

According to the expert opinions and the characteristics of elderly stroke, the intervention program was adjusted as follows: older stroke patients were prone to coughing and choking when eating raisins in the traditional mindful diet, so the program was adjusted to sour date cake or chocolate; In addition, in the intervention program, other members of the group-based ACT intervention team would assist in completing the game, considering if the older population had physical impairment.

### Eligibility criteria

Inclusion criteria are: (1) conforming to the World Health Organization diagnostic criteria of stroke and confirmed by magnetic resonance imaging (MRI) or computed tomography (CT); (2) age ≥ 60 years old; (3) disease duration of more than half a year and having passed the acute stage and standard treatment [26]; (4) reporting a clinically significant level of psychological distress (Hamilton Depression Scale scored ≥ 8); (5) having the ability to communicate on a daily basis; (6) agreeing to participate and provide informed consent; and (7) having the ability to use WeChat, which is a multi-purpose social media, messaging and payment app developed in China.

Exclusion criteria are: (1) having other organic encephalopathy such as respiratory, cardiovascular, digestive and other serious physiological diseases; (2) having a history of alcohol or other psychoactive substance abuse or dependence; (3) having dementia, a recognized complication of stroke; (4) limb function weakened, and could not tolerate sitting for one hour.

### Sample size calculation

In this study, the sample size was calculated using PASS 16.0 Software. The sample size estimation formula of the mean of the two groups is adopted for calculation: The sample size ratio of the two groups was 1:1, that is, the Group Allocation was Equal(N1 = N2); Refer to Xiuli et al.s’ study [27], The control group and intervention group of HAMD scores, respectively (8.9 ± 4.0) and (6.5 ± 2.9). The α is the type I error probability, i.e. the test level or significance level, which is 0.05 on both sides in this study, the confidence level is 95%, $${u}_{\alpha }$$ is 1.96. The β is class II error, which is 0.1, $${u}_{\beta }$$ is 1.28.$${n}_{1}={n}_{2}=2{\left[\frac{\left({u}_{\alpha }+{u}_{\beta }\right)}{\delta /\sigma }\right]}^{2}+\frac{1}{4}{{u}_{\alpha }}^{2}$$

According to the above formula, the sample size of each group was about 25 cases. Taking into account the sample loss and other problems, each group was expanded by 30%. Therefore, the final sample size for each group was approximately 33 cases, a total of 66 cases were required.

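### The printed sample-size formula with its stated inputs gives about 46 per group (32 to 60 depending on the SD used), not 25, so 66 patients do not deliver the stated beta of 0.1 for HAMD

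*Protocol article*

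**What the plan says.** All the ingredients are in the protocol article, section Sample size calculation:

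- Method: "The sample size estimation formula of the mean of the two groups is adopted for calculation". The printed formula is n1 = n2 = 2[(u_alpha + u_beta)/(delta/sigma)]² + u_alpha²/4.
- Allocation: "the Group Allocation was Equal(N1 = N2", that is 1:1.
- Alpha: "which is 0.05 on both sides in this study", with u_alpha = 1.96.
- Type II error: "The β is class II error, which is 0.1", with u_beta = 1.28. This is equivalent to 90% power.
- Means and SDs, from a cited earlier study: "The control group and intervention group of HAMD scores, respectively (8.9 ± 4.0) and (6.5 ± 2.9".
- Result: "According to the above formula, the sample size of each group was about 25 cases".
- Loss step: "Taking into account the sample loss and other problems, each group was expanded by 30" per cent, giving about 33 per group and 66 in all.

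The section does not say which value was used for sigma. The total reappears in the abstract ("A total of 66 stroke survivors will be randomly assigned to wait-list control group or intervention group") and fixes the list of 66 random numbers described under Randomization.

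**The concern.** The article states every input except the choice of sigma, and it attributes the answer to the printed formula, so a reader can check it directly. If 25 does not follow, the basis for 33 per group and 66 in total falls with it, because no other justification of the sample size is given.

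At stake is how a non-significant HAMD result would be read. With beta stated as 0.1, readers would take it as coming from a comparison that had one chance in ten of missing a 2.4-point difference. If the true chance is two or three times that, the result carries much less weight than the protocol implies.

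**Working it through.** **Inputs** (all from Sample size calculation): delta = 8.9 − 6.5 = 2.4; SDs 4.0 and 2.9; u_alpha = 1.96; u_beta = 1.28, so u_alpha + u_beta = 3.24; correction term 1.96²/4 = 0.96.

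**Trying to reproduce 25.** With the usual pooled SD for equal groups:

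- sigma = √[(4.0² + 2.9²)/2] = √12.205 = 3.494
- delta/sigma = 2.4/3.494 = 0.687
- n = 2 × (3.24/0.687)² + 0.96 = 44.49 + 0.96 = 45.45, so **46 per group**

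Because sigma is undefined, the other candidates from the stated SDs are:

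| sigma | formula result | per group |
|---|---|---|
| 2.9 (intervention SD) | 31.61 | 32 |
| 3.45 (mean of the two SDs) | 44.35 | 45 |
| 3.494 (pooled) | 45.45 | 46 |
| 4.0 (control SD) | 59.28 | 60 |

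None gives 25. Solving the formula backwards, n = 25 requires sigma = 2.4 × √[(25 − 0.96)/2]/3.24 = 2.57, below both stated SDs. With the pooled SD kept, it requires delta of about 3.26, which is not stated anywhere.

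**Does a slip in another input explain it?** Values near 25 appear only if something stated is changed:

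- one-sided alpha and 80% power: 26.9 with the pooled SD, 26.2 with the mean SD
- one-sided alpha, 90% power, SD 2.9: 25.7
- two-sided alpha, 80% power, SD 2.9: 23.9
- factor 2 omitted, pooled SD: 23.2
- factor 2 omitted, one-sided alpha, 90% power, SD 4.0: 24.4

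Each contradicts the stated alpha, the stated beta, the printed formula or the pair of SDs. The document does not show which, if any, occurred.

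**Power of the numbers adopted.** Two-sided 0.05, difference 2.4, pooled SD 3.494:

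| evaluable per group | t-test | normal approximation |
|---|---|---|
| 25 | 66% | 68% |
| 33 | 78% | 80% |
| 46 | 90% | 91% |

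Allowing for unequal variances (Welch) changes the t-test figures by no more than about 0.2 percentage points. The type II error is therefore about 22% at 33 per group and about 34% at 25, against a stated 10%.

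**The loss step.** 25 × 1.3 = 32.5, rounded to 33, so the expansion is carried out as described. Going from 33 down to 25 covers a loss of 1 − 25/33 = 24%. If a 30% loss rate were expected, which is an assumption and not in the text, 33 × 0.7 = 23 per group would remain, with power of about 63%.

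**The case against.** Four objections deserve an answer.

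1. **Sigma is not defined, so 46 is not the only possible answer.** This is correct, and 46 should be read as the pooled-SD result within a range of 32 to 60. It does not rescue 25, which lies below the whole range. In the most favourable case, SD 2.9 in both arms and nobody lost, 33 per group would give about 91% power. That sets aside the stated control SD of 4.0 and the plan's own allowance for loss.

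2. **The planned analysis is more efficient than a two-sample comparison.** The section Statistical analysis plans a repeated-measures mixed model with baseline-adjusted differences, which can lower the required number by a factor of roughly 1 − r², where r is the baseline-to-follow-up correlation. The document gives no r. If r were 0.5 (an assumption), the need would be 44.49 × 0.75 + 0.96 = 34.3, so 35 per group. This stands as a limit on what the power figures mean: they describe the calculation as printed and are not the power of the final model. It does not explain a result said to come from the printed formula, which includes no such adjustment.

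3. **The loss allowance is not an error.** A reader might infer that the trial expects 30% loss, that the allowance should have been 25/0.7 = 36, and that planned power is therefore only about 63%. The text does not support this. It describes an expansion of each group by 30%, performs that expansion correctly and states no expected loss rate.

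4. **HAMD is not the primary outcome.** This is true: the article lists AAQ-II as primary and HAMD as secondary. A reader might infer that the primary comparison has 78% or 66% power. The calculation contains no AAQ-II figures, so nothing here supports a power statement for it in either direction.

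**Conclusion.** The point stands as an arithmetic error in the only sample-size justification given. The printed formula and stated inputs yield 46 per group with the pooled SD, and at least 32 under any SD taken from the two stated values. The figure of about 25 is too far off to be rounding.

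The stated beta of 0.1 is consequently not met by the plan's own method. For a 2.4-point HAMD difference, the miss rate is more than twice the stated one with all 33 per group evaluable, and more than three times at the 25 per group that the plan treats as sufficient. These multiples assume the pooled SD and an unadjusted comparison of HAMD at a single time point. They do not extend to the primary outcome, nor to a 30% loss that the article does not state.

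**What to change.** In Sample size calculation:

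- Define sigma (for example, the pooled SD of 3.49) and correct the formula result from 25 to 46 per group.
- If 66 patients are kept, withdraw the beta of 0.1. State that, for a HAMD difference of 2.4 with SD 3.49, power is about 78% with all 33 per group evaluable and about 66% with 25 per group evaluable.
- State that these figures are for an unadjusted comparison of HAMD, a secondary outcome, and not for the primary AAQ-II.
- State the loss rate that the 30% expansion is meant to cover. The margin from 33 to 25 is about 24%. If 30% loss is really expected, give the figure for 23 per group (about 63%) and label it as resting on that assumption.

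Keeping 66 costs wording only: no extra patients and no change to the randomisation list, though the stated power becomes less favourable. The alternative of keeping beta at 0.1 means enlarging the trial. On the plan's own 30% expansion, 46 × 1.3 = 59.8, so 60 per group and 120 in total, nearly double the present number.

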### Randomization

Randomization is performed by an independent researcher. Patients who volunteered for the study were numbered in the order of their admission. Sixty-six random numbers were generated using IBM SPSS Statistics for Windows (Version 26.0 Armonk, NY: IBM Corp) in descending order. Digits 1st through 33rd of the random-number sequence were numbered as the wait-list control group, and the remaining digits 34th through 66th were numbered as the intervention group.

### Interventions

#### Wait-list control group

The wait-list control group will receive TAU treatment for eight weeks, and the intervention will take place in a separate room in the inpatient building of the supporting unit, away from the ACT intervention site. When the intervention group has completed all the ACT procedures, the wait-list control group will receive the same ACT intervention as the intervention group. The TAU intervention is as follows. (1) Disease knowledge guidance, including introducing to patients the causes of stroke, how to identify stroke, clinical manifestations, treatment methods and other knowledge, so that patients can have a more comprehensive understanding of stroke; (2) Medication guidance and health education, including the mode of medication, time of medication, precautions for medication, possible side effects after medication and how to deal with them; (3) Basic psychological guidance, including counseling, persuasion and other forms, enabling patients to feel respect and care, increase their trust in medical staff, and rebuild their confidence to resume normal life; (4) Rehabilitation guidance, including rehabilitation training timing, rehabilitation training methods and precautions; (5) Psychological nursing, including encouraging patients, timely answering their doubts in the process of rehabilitation treatment, reducing their fear of disease, and establishing their confidence in early recovery.

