### Intervention group

All interventions received by the intervention group were carried out in a separate activity room with an area of 20 m^3^ to ensure no interference. The activity room will be equipped with seats approximately, drinking water, and other necessary items. Moreover, necessary first-aid items will be also provided to ensure patient safety. The research team will provide materials and related things for ACT. Throughout the intervention, the health care workers will keep the patient safe at all times.

For the intervention group, group-based acceptance and commitment therapy intervention will be given for 8 weeks in addition to TAU, which will be completed by 2 graduate students, both of whom were systematically trained group-based ACT consultants, and will also lead the group consultation activities. Each group-based ACT intervention will consist of 10 ~ 12 people, once a week for 40 to 60 min, for 8 consecutive weeks. The content consists of eight sessions: confronting the agenda, accepting everything, objectively observing cognition, the hours, feeling yourself, identifying your value, looking forward, and review. The specific intervention content of each module is shown in Table 1.

**Table 1 Tab1:** An overview of the group-based ACT program for older stroke survivors

Session	Content
Confronting the Agenda	Start with an “Ice-breaking tour” (5–10 min) Patient self-introduction (10–15 min) Introduction of ACT team members and content (5 min) Mindfulness exercises (10–15 min) Home task (5 min)
Accepting everything (Acceptance)	Begin with a mindfulness exercise and homework review (5–10 min); Watch a video of sinking into a swamp (10-15 min); Play the game “Chinese Finger Glove” (10–15 min); Share and summarize (10–15 min); Home task (5 min).
Observing cognition objectively (Cognitive Defusion)	Homework review (5–10 min); Play the video “Passengers on the Bus” (5–10 min); Play the game “Folder push” (10 to 15 min); Share and summarize (10–15 min); Home task (5 min).
The Hours (Being Present)	Begin with a review of last week’s homework (5-10 min); Mindful eating (10 min); Mindful breathing exercise (10-15 min); Share and summarize this activity (5–10 min); Home task (5 min).

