### Blinding

The researcher conducting baseline assessments (T0) will be blinded to participant treatment allocation, as participants will also be blinded to randomization after the baseline assessment (T0). It is not possible for the treating psychologists providing the intervention to be blinded. However, an independent assessor who will join to complete the post-treatment (T1) and one-month follow up assessment (T2), will be blinded to the condition. The success of blinding will be assessed by having independent assessors (i) indicate which condition they thought the participant will be randomly assigned to and (ii) indicate whether the participant will disclose their treatment condition or not. Data analysis will be undertaken by a graduate student with no direct contact with the individual research group to remain blinded to the treatment conditions. It is expected that unblinding will be not needed for independent assessors or statisticians, therefore in this study, unblinding is not permissible.

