### Statistical analysis

The statistical analysis of this study can be divided into four parts. Firstly, the IBM SPSS Statistics for Windows (Version 26.0 Armonk, NY: IBM Corp) would be used in this study. Data processing was performed to review missing data, followed by screening for normality for all outcome measures and for each treatment group. Secondly, inter-group comparisons were performed prior to the main analysis, and differences between baseline groups were analyzed using Chi-square test and independent sample T-test to verify the success of randomization. If the relevant data did not conform to a normal distribution, the generalized estimation equation (GEE) would be used for analysis. In addition, a preliminary analysis would be performed on an intention-to-treat basis using Generalized linear mixed model (GLMM) to investigate the differential effects of each treatment condition. For the post-treatment analysis in the three treatment conditions, the analysis will focus on the linear time effect, treatment conditions and interaction. Finally, a linear mixed model repeated measures (MMRM) was used to study inter-group differences with primary and secondary outcome measures as dependent variables. The model would include processing conditions and time as classification variables, as well as their interaction effects. The baseline adjusted mean difference between groups at each time point would be calculated using a 95% confidence interval, with the value of alpha set at 0.05. The analysis would focus on the estimated mean differences between primary and secondary outcome indicators at different time points.

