### Ethical considerations and dissemination

Throughout the study, ethical requirements will be strictly observed at all stages. We will maintain the right to information of the research objects, abide by the principle of confidentiality, and formulate relevant risk avoidance and disposal plans.

Follow the principle of informed consent. We will fully explain to the participants information about the purpose, content, potential risks, direct or indirect benefits and other information of the research to ensure that they understand and voluntarily participate in the study and sign informed consent forms.Follow the principle of confidentiality. All personal information obtained during the research will be kept confidential and used for research purposes only. Upon completion of the research, the research materials will be destroyed immediately. All publications and papers based on the data from this study will not disclose any identifiable personal information about the subject.Risk avoidance and disposal plan. (i)In the process of data collection and intervention, researchers will give detailed explanations, personal demonstrations and guidance to measurement and exercise-related movements, and teach participants to do the relevant movements safely to avoid unnecessary injuries. At the same time, rest is arranged as appropriate by observing and inquiring about participants’ status. (ii)Participants are informed that in case of adverse events, caregivers and project staff should be notified immediately, and project staff should assist in contacting the relevant medical units for treatment, and report to the ethics Committee. (iii)In the whole process of on-site intervention, the medical staff will ensure safety and avoid accidents.Follow the principle of equal treatment in the control group. After the intervention, if the intervention proves to be effective, the same intervention and content instruction will be given to the wait-list control group.

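### The two rules for giving ACT to wait-list controls conflict, and neither keeps controls off ACT until the one-month assessment (T2)

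*Protocol article*

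**What the plan says.** The protocol article describes ACT for controls in two places.

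- **Interventions, Wait-list control group.** The control condition has a fixed length: "The wait-list control group will receive TAU treatment for eight weeks". The crossover follows without any condition: "When the intervention group has completed all the ACT procedures, the wait-list control group will receive the same ACT intervention as the intervention group".
- **Ethical considerations and dissemination.** Here the offer is conditional: "After the intervention, if the intervention proves to be effective, the same intervention and content instruction will be given to the wait-list control group".

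Three other sections fix the timetable and the analysis.

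- **Intervention group.** ACT is delivered in groups of 10 to 12, "once a week for 40 to 60 min, for 8 consecutive weeks".
- **Study design.** Outcomes are assessed at T0, T1 (post-treatment) and "one-month follow up (T2) for both groups". Participants are recruited "using convenience sampling between December 2022 to March 2023".
- **Statistical analysis.** "The baseline adjusted mean difference between groups at each time point would be calculated using a 95% confidence interval". The section also refers to a linear time effect and its interaction with treatment.

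No section shown says that controls stay off ACT until T2, or what controls receive between the end of their eight weeks and T2.

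**The concern.** A wait-list control is a valid comparator only while it is still waiting. If controls have begun ACT by T2, the T2 contrast no longer compares ACT with TAU. It compares ACT given at once with ACT given later. If ACT works, the controls improve and the difference narrows even when the intervention arm keeps all of its gain, so a lasting benefit could be read as one that fades. T2 is the only assessment after T1, so nothing later in the trial could show which reading is right.

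The conflict also matters in its own right. If ACT is not shown to work, one section still promises it to controls and the other withholds it. Staff cannot follow both.

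**Working it through.** There is no figure in the plan to reproduce here. The check compares the two rules and then builds the timeline.

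**1. The rules side by side**

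| | Wait-list control group section | Ethical considerations section |
|---|---|---|
| Do controls get ACT? | Yes, unconditionally | Only if ACT is shown to work |
| Trigger | Intervention group has finished ACT | A finding of effectiveness |
| Start relative to T2 | Not stated | Not stated |

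The first row is a direct contradiction. On timing the rules differ in what they permit. The first allows a start once ACT is complete. The second points to a start after the analysis, since the article describes no interim look.

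**2. Upper end of exposure**

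Inputs: ACT lasts 8 weekly sessions (Intervention group); control TAU lasts 8 weeks (Wait-list control group); T2 is one month after treatment, taken here as 4 weeks.

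- Intervention ACT ends, and T1 falls, at week 8.
- T2 falls at week 8 + 4 = 12.
- If all groups run together and controls start at once, sessions before T2 = 12 − 8 = about 4 of 8.

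**3. Lower end of exposure**

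The trigger refers to the intervention group as a whole, and 33 patients in groups of 10 to 12 means about three groups (33/12 = 2.75; 33/10 = 3.3). Assume:

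- three intervention groups, k = 0, 1, 2, starting s weeks apart;
- controls enrolled alongside each group;
- control groups later staggered by the same s;
- a delay of g weeks between the arm finishing and the first control group starting.

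Then:

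- the last intervention group finishes at week 2s + 8;
- control group k starts ACT at week 2s + 8 + ks + g;
- its T2 is at week ks + 12;
- sessions by T2 = max(0, (ks + 12) − (2s + 8 + ks + g)) = max(0, 4 − 2s − g).

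Results:

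- s = 0, g = 0: 4 sessions
- s = 1, g = 0: 4 − 2 = 2 sessions
- s = 2, g = 0: 4 − 4 = 0 sessions
- s = 0, g = 4: 0 sessions

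Recruitment from December to March is about 17 weeks, so staggers of two weeks or more are feasible. The values of s and g, and the pattern of control starts, are assumptions; the text gives none of them. From the text, exposure can be bounded only at 0 to about 4 of 8 sessions.

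**4. What the exposure reaches**

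T1 comes before any control ACT under either rule, so the T1 difference is untouched. The T2 difference and any time-by-treatment term that uses T2 are open to the bias.

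**The case against.** **The rules can be reconciled on timing.** The Wait-list control group section sets an order, not an immediate start. A start after the final analysis would satisfy the timing of both rules and give no exposure. This stands, and it is why the text can be said only to permit early crossover. It does not remove the problem, because no wording requires the later start, and the conflict over whether controls get ACT at all remains.

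**Timing may be given elsewhere.** Fig. 1 is a natural place for it and is not shown, and a journal article condenses a fuller protocol. This also stands as a caution. Two stated rules that disagree are, however, more than omitted detail.

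**No maintenance objective is stated.** The aim and hypotheses do not mention maintenance, and the bias would be conservative. Both points are fair and limit the importance of the issue. The analysis section still plans the T2 contrast.

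**Stronger readings that a reader might infer.**

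- *At least the last-treated controls must be exposed.* This follows only if all controls start in the same week, as soon as the intervention arm finishes. With control groups staggered by two weeks or more, nobody is exposed.
- *Half the sessions means half the effect is lost.* The documents give no dose-response, so no percentage attenuation or loss of power can be derived.
- *The ban on unblinding proves that crossover comes after T2.* The statement in Blinding, "therefore in this study, unblinding is not permissible", concerns assessors and statisticians. It does not date the crossover.

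**Conclusion.** The point holds in a limited form. The two sections contradict each other on whether controls receive ACT, and neither fixes the start relative to T2. As written, the Wait-list control group section permits a start at about T1, roughly four weeks before T2.

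Exposure by T2 lies between 0 and about 4 of 8 sessions, assuming weekly sessions and a four-week month. If ACT is beneficial, any exposure biases the T2 results toward no effect; it would not create a false benefit. The size of the bias cannot be computed from the documents. Fig. 1 may already place the crossover after T2, in which case only the wording conflict remains. The matter should be fixed because the remedy is cheap and the affected comparison cannot be recovered once controls have started ACT.

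**What to change.** Amend the Wait-list control group and Ethical considerations sections to state one rule: controls stay on TAU, and wait-list ACT starts only after each control's T2 assessment. State in the same place whether the offer depends on proven effectiveness, and check that Fig. 1 agrees.

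The cost is one sentence in each section, with no added patients or visits. Controls may wait about one month longer for ACT.

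If the earlier start is kept, base the ACT-versus-TAU conclusion on T1 for the AAQ-II and the secondary outcomes. Report T2 as a randomised comparison of immediate with delayed ACT, and give the number of ACT sessions controls had received by then. The cost of that choice is that T2 no longer says whether the benefit over TAU lasts.
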